## Abstract

**Background:**

Current projections indicate that there will be a significant increase in the number of people with dementia in Ireland, from approximately 40,000 at present to 100,000 by 2036. Psychosocial interventions, such as reminiscence, have the potential to improve the quality of life of people with dementia. However, while reminiscence is used widely in dementia care, its impact on the quality of life of people with dementia remains largely undocumented and there is a need for a robust and fair assessment of its overall effectiveness. The DementiA education programme incorporating REminiscence for Staff study will evaluate the effectiveness of a structured reminiscence-based education programme for care staff on the quality of life of residents with dementia in long-stay units.

**Methods/Design:**

The study is a two-group, single-blind cluster randomised trial conducted in public and private long-stay residential settings in Ireland. Randomisation to control and intervention is at the level of the long-stay residential unit. Sample size calculations suggest that 18 residential units each containing 17 people with dementia are required for randomisation to control and intervention groups to achieve power of at least 80% with alpha levels of 0.05. Each resident in the intervention group is linked with a nurse and care assistant who have taken the structured reminiscence-based education programme. Participants in the control group will receive usual care. The primary outcome is quality of life of residents as measured by the Quality of Life-AD instrument. Secondary outcomes include agitation, depression and carer burden. Blinded outcome assessment is undertaken at baseline and at 18-22 weeks post-randomisation.

**Discussion:**

Trials on reminiscence-based interventions for people with dementia have been scarce and the quality of the information arising from those that have been done has been undermined by methodological problems, particularly in relation to scale and scope. This trial is powered to deliver more credible and durable results. The trial may also convey process utility to a long-stay system in Ireland that has not been geared for education and training, especially in relation to dementia. The results of this trial are applicable to long-stay residential units in Ireland and internationally.

**Trial registration:**

Current Controlled Trials ISRCTN99651465

## Background

Dementia is a chronic progressive debilitating disease that is largely a disorder of old age. It is characterised by widespread impairment of mental functioning, progressive memory loss, language difficulties, confusion and disorientation. These impairments are often accompanied by behavioural and psychological disturbance [1]. The behavioural disturbances associated with dementia are defined as symptoms of disturbed perception, altered thought content, mood and behaviour [2].

Studies on the prevalence of dementia indicate a sharp rise with age, doubling with every 6.3 year increment in age in Western Europe [3]. Current projections indicate that there will be a significant increase in the number of people with dementia in Ireland, from approximately 40,000 at present to 100,000 by 2036 [4]. International estimates suggest that approximately half of those with dementia will be cared for in a residential care setting at some point during the disease [5]. There is limited information on prevalence rates for dementia within long-stay settings, but what is available suggests that the majority of long-stay residents are likely to have dementia. It is estimated, for example, that between 50% and 80% of residents in various types of residential care settings in the UK may have dementia [6]. Recent small-scale estimates for Ireland suggests that a large majority of long-stay residents have cognitive impairment (up to 89%), the majority of whom are likely to have undiagnosed dementia [7]. This data is at variance with official statistics for Ireland, which suggests that only 26% of residents in long-stay care have dementia [8].

The Action Plan for Dementia (APD) for Ireland [9] advocates a person-centred approach to care in both community and long-stay settings that emphasises the individual needs of the person with dementia. Such an approach focuses on what people are still able to do and remember, and on maintaining the individuality of the person with dementia [10]. Promoting a sense of well-being among older people with dementia is enhanced by creating a supportive social environment, thereby enabling people to communicate and connect with family and friends [10,11]. Integrating evidence-based psychosocial approaches with medical and nursing care models of service delivery is key to the person-centred approach. If healthcare professionals are to develop the skills necessary for such an approach to care delivery, education about dementia and staff training in psychosocial treatments are essential [4,9]. Unfortunately, residential care staff in Ireland do not always have the skills and knowledge necessary to respond effectively to the individual needs of residents with dementia [12].

Psychosocial interventions have the potential to improve the quality of life of people with dementia and those who care for them, and a number of systematic reviews have been undertaken [13-15], including Cochrane reviews of specific approaches [16,17]. Reminiscence is a psychosocial intervention commonly used in dementia. It involves the discussion of past activities, events and experiences with another person or group of people, usually with the aid of tangible prompts such as photographs or other familiar items. One factor contributing to the popularity of reminiscence is that it can be used with early memories, which remain relatively intact for people with dementia, thus drawing on the person's preserved abilities rather than focusing on level of impairment induced by the illness. Although used extensively, little is known about the effectiveness of reminiscence as a care intervention for people with dementia [18], [19], [20].

Most studies that have examined the effectiveness of reminiscence have employed qualitative, descriptive or observational designs, with few robust experimental designs having been undertaken [19,21-23]. The most recent Cochrane systematic review of reminiscence therapy in dementia [19] showed that there was evidence of an improvement in cognition and in general behaviour in people with dementia, as well as a decrease in caregiver strain following reminiscence therapy. Five randomised controlled trials were included in this Cochrane review, although only four, with a combined total of 144 participants, had extractable data. The studies were small in scale, incorporating diverse forms of reminiscence therapy, resulting in inconclusive evidence on overall effectiveness. Therefore, the effectiveness of reminiscence on the quality of life of people with dementia remains uncertain, pointing to the need for a more robust and fair assessment of interventions using treatment protocols that set out clearly the type of reminiscence being undertaken, overall objectives, process and outcomes.

Our proposed DementiA education programme incorporating REminiscence for Staff (DARES) intervention is designed to address some of the unanswered questions regarding the effectiveness of reminiscence in the care of people with dementia. The main component of DARES is a structured education reminiscence-based programme for staff which is delivered at the level of the long-stay residential unit to dyad combinations of nursing and care staff who are directly engaged in the care of specified people with dementia.

In this study, we define reminiscence as the deliberate use of prompts, including photographs, smells, music and questioning, to promote the recall of pleasant memories. We view reminiscence as a one-to-one interaction between the person with dementia and a staff member, except where working in a small group is more appropriate, as determined by the capacity and needs of the individual with dementia. Reminiscence is both planned, i.e. where reminiscence is the specific focus of the interaction with the person with dementia, and spontaneous, i.e. the opportunistic use of reminiscence while providing nursing care. The aim of using reminiscence with people with dementia is to stimulate the person, provide enjoyment and foster a sense of achievement and self-worth. The anticipated outcomes for people with dementia of using reminiscence are improvement in the person's quality of life, behaviour and mood.

## Aim

The aim of the DARES study is to evaluate the effectiveness of a structured education reminiscence-based programme for staff on the quality of life of residents with dementia in long-stay residential units. The study has three main objectives:

1. To develop a comprehensive structured education reminiscence-based programme for staff that is specifically orientated toward enabling planned and spontaneous reminiscence to take place as part of the care of people with dementia.

2. To evaluate the impact and effectiveness of the structured education programme within the context of a cluster randomised trial.

3. To understand participants' qualitative perceptions of the education programme, their experience of care following the intervention and its impact on their lives.

## Methods/Design

The DARES study is a two-group, single-blind cluster randomised trial conducted in public and private long-stay residential settings in Ireland (see Figure 1). Randomisation to control and intervention is at the level of the long-stay residential unit. Care staff within the long-stay residential units allocated to the intervention group receive the structured education reminiscence-based programme. Trained staff use reminiscence with eligible consenting residents within the intervention long-stay settings. Residents in long-stay settings allocated to the control group receive usual care. Blinded outcome assessment is undertaken at baseline and at 18-22 weeks post randomisation. A comparison of outcomes between the intervention and control sites is made to examine if differences exist, and to what extent, between control and experimental groups. Ethical approval has been granted by the Research Ethics Committee of the National University of Ireland, Galway and from each of the appropriate county/hospital-based ethics committees responsible for the public long-stay units in the trial.

**Figure 1 F1:**
[figure not shown]
**DARES Methodology**.

We used methods for standard sample size estimates for trials that randomised at the level of the individual [24] adjusting for clustering by inflating sample size estimates by the design effect given by $1+(\bar{n}\text{-1})\rho$, $\bar{n}$ where is the average cluster size, and ρ is the estimated intraclass correlation coefficient (ICC) [25]. Sample size estimates are based on the primary outcome of quality of life of people with Alzheimer's disease as measured by the Quality of Life-Alzheimer's disease (QOL-AD) scale. This instrument consists of two versions; one completed by the person with dementia (care recipient) and the other by the caregiver [26,27]. We chose the care recipient version to estimate sample size for the DARES trial, expressed as the mean rate difference between intervention and control groups.

Based on a mean QOL-AD score of 32.5 for people with dementia in residential care homes [28] and an ICC value of 0.1 identified from pilot work on reminiscence groups for people with dementia for the REMCARE Trial [29], a total of 18 residential units are required, each containing 17 people with dementia, to detect a 4 point difference in mean QOL-AD scores between control and experimental groups, for power of at least 80% with alpha levels of 0.05. This calculation allows for a loss to follow-up of 20% of residents and up to 3 residential units. ICC values lower than 0.1 would increase the power of the study.

### Participants

Public and private long-stay units across the western half of the Republic of Ireland who meet the eligibility criteria were invited to participate in the DARES study. Units are eligible to participate if they have 17 residents with dementia who agree, either directly or through proxy, to take part in the study. This aggregates to a total of 306 residents in the study. Residents are eligible for participation if they have lived in the residential unit for at least one month and are likely to be there for the duration of the study. Given the reality that formal clinical diagnosis of dementia in residential care is rare in Ireland, diagnosis of dementia in residents is determined in any one, or more, of the following ways:

• A formal diagnosis of dementia determined by the DSM-1V or ICD-10 criteria for dementia [30,31]

• Any other diagnosis of dementia by a medical clinician

• Resident is on anti-Alzheimer's medications, including Aricept (donepezil), Ebixa (memantine) and Exelon (rivastigmine)

• Nurses' judgement and/or nursing records advise that the person has dementia

Residents are excluded from the study if they have a significant sensory impairment or an acute physical illness that, in the judgement of the appropriate nursing staff, impairs their ability to participate.

Each nurse and care assistant participating in the study will usually have worked within the care setting for at least three months and be likely to continue working there for the duration of the trial. Five dyads are required to participate in each unit. Each of the participating dyads are allocated three-four participating residents with dementia with whom they implement reminiscence for the duration of the study.

### Randomisation

Randomisation to control and intervention is at the level of the long-stay residential unit. The random allocation sequence is generated using a computer generated random number list (the Mersenne Twister, Stat Direct). Randomisation is 1:1 ratio and is stratified by public and private residential units to ensure an appropriate representation of public and private facilities; a ratio of one third public to two thirds private reflects the overall distribution of beds in the region. Concealment of group allocation is achieved by giving the responsibility for sequence generation and group allocation to a researcher with statistical expertise who is independent of the study and its investigators.

The independent statistical researcher will create a consecutive list of 12 unnamed private units, numbered 1-12, and a separate list of 6 unnamed public units, numbered 1-6. A random allocation sequence is generated and each unnamed unit is assigned a trial allocation based on the sequence. As participatory units agree to enter the trial, the research team will provide the independent statistical researcher with an anonymised list of unit(s) that meet the eligibility criteria. The independent statistical researcher will then document the unique identification code assigned to that unit in the next 'unnamed' position in the randomised public or private list and release the corresponding group allocation for the unit.

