## Analyses

### Quantitative Data

The focus is on the long-stay care setting with the resident as the unit of analysis. Analyses is by intention to treat, with all available data included. Quantitative data is analysed, in aggregate, using the Statistical Package for the Social Sciences (SPSS, v17). Data is entered into SPSS, coded and cleaned. Demographic characteristics of staff and of residents are described using percentages, measure of central tendency (means or medians) and measures of variation (standard deviations or ranges). Differences in mean scores are examined using analysis of variance and 2-sample independent t-tests. Relative risks with 95% confidence intervals are calculated with the control group as the reference. Multi-level modelling is used to address the issue of clustering within randomised groups.

Analysis of covariance is used to adjust for baseline differences in outcome variables. Test statistics based on chi-square are divided by the design effect while test statistics based on the t-test or z-tests are divided by the square root of the design effect. Whilst every effort is made to exclude all confounders at the design phase of the study, this may not always be possible. The analysis of data will, therefore, include the search for and control of nuisance variables, for which adjustments had not been made. The change in the primary response variable is modelled across the within subject factors (T_1 _and T_2_), adjusting for explanatory variables as required.

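### The public/private stratum used to randomise units is not pre-specified in the analysis; precision may be lost if the two types of unit differ in quality of life

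*Protocol article*

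**What the plan says.** Under Randomisation, the article says: "Randomisation is 1:1 ratio and is stratified by public and private residential units". The independent statistical researcher works from two separate lists, 12 private and 6 public units. The stated purpose is proper representation of the two kinds of facility. No blocking within the lists is mentioned.

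Under Analyses, Quantitative Data, the article lists ANOVA and two-sample t-tests, division of test statistics by the design effect or its square root, and multi-level modelling for clustering. It adds: "Analysis of covariance is used to adjust for baseline differences in outcome variables". Public/private is not named in any of these. Two general provisions remain: the change in the primary outcome may be adjusted for explanatory variables where needed, and the analysts will look for nuisance variables not already adjusted for.

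The sample size text (Methods/Design, below Figure 1) aims at a QOL-AD difference of 4 points, with 80% power or more at the 5% level. Its result is: "a total of 18 residential units are required, each containing 17 people with dementia". It takes no credit for stratification.

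**The concern.** A stratification factor is known before any outcome is seen and is part of the design. If arms are balanced within strata, the stratum difference cancels from the treatment contrast. A model without the stratum still counts that difference as unexplained variation between units. The estimated standard error is then larger than the true one, the test rejects too rarely under the null, and power is lost.

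This matters more here than in a large individually randomised trial, because with 18 units the between-unit variation largely sets the precision. The wording on nuisance variables would also let the one design factor enter only by a data-driven choice, although it could be fixed now at almost no cost.

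**Working it through.** **The plan's own figure.** 18 × 17 = 306, which agrees with the article. The 18 units cannot be derived, because the text gives a mean ("Based on a mean QOL-AD score of 32.5 for people with dementia in residential care homes") but no SD. After the allowed losses ("This calculation allows for a loss to follow-up of 20% of residents and up to 3 residential units") there are 15 units of 17 × 0.8 = 13.6 residents. The design effect is 1 + 12.6 × 0.1 = 2.26, and the effective n per arm is 15 × 13.6 / 2.26 / 2 = 45.1. By the normal approximation, 80% power for 4 points holds if the SD is at most 4 × √(45.1/2) / (1.960 + 0.842) = 6.78. The stratum plays no part in this.

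**Inputs for the check.** From the article: 12 + 6 units, 1:1 allocation, and "an ICC value of 0.1 identified from pilot work on reminiscence groups for people with dementia". Assumed: two-sided 5% test, all 18 units kept, 14 residents per unit (13.6 rounded), effect 0.55 SD, 6:6 and 3:3 allocation, and a public/private gap of 0, 0.25 or 0.5 SD added to the ICC of 0.1. Only the differences in power matter below; the absolute levels depend on the assumed 0.55 SD.

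**Standard error without baseline.** Variance of a unit mean: 0.1 + 0.9/14 = 0.1643. With the stratum in the model, SE = √(4 × 0.1643 / 18) = 0.191. Without it, the residual sum of squares gains gap² × 18 × (1/3) × (2/3) = 4 × gap², spread over 16 df, so the residual variance rises by gap²/4.
- Gap 0.25: 0.1643 + 0.0156 = 0.1799; SE 0.200, 5% too large.
- Gap 0.5: 0.1643 + 0.0625 = 0.2268; SE 0.224, 17% too large.

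**Power by simulation of unit means (8,000 to 40,000 trials per setting), without v with the stratum.**

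| Analysis | Gap 0 | Gap 0.25 SD | Gap 0.5 SD |
|---|---|---|---|
| No baseline | 77.0 v 76.7% | 74.3 v 76.7% | 65.1 v 76.7% |
| Baseline, correlation 0.3 | 78.8 v 78.4% | 76.9 v 77.6% | 73.8 v 77.4% |
| Baseline, correlation 0.5 | 85.0 v 84.2% | 83.8 v 83.8% | 83.1 v 84.2% |
| Baseline, correlation 0.7 | 94.4 v 94.3% | 95.2 v 94.9% | 94.9 v 94.8% |

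The baseline rows assume that the same gap is present at baseline and follow-up; the article gives no correlation. Without baseline, a 0.5 SD gap brings the type I error of the unstratified test down to about 2%. With baseline it is 4.0 to 4.7%, and the SE is 1 to 6% too large.

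**If the gap is part of the ICC of 0.1.** A 0.5 SD gap with a one-third to two-thirds split adds 0.25 × 2/9 = 0.056 to the between-unit variance, so the total ICC in the table above is (0.1 + 0.056)/1.056 = 0.15. Holding the total at 0.1 instead (SD 6.78, 18 × 17, no baseline, noncentral t), the unadjusted power stays at 85.2%. Adding the stratum gives 84.8, 87.1, 90.4 and 95.4% if it explains 0, 10, 25 and 50% of the between-unit variance. Seen this way, omission forgoes a gain and does not reduce planned power.

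**If allocation within lists is unblocked.** With simple randomisation and no baseline, the unstratified type I error stays near 5%. Power without v with the stratum is about 61 v 71% at a 0.5 SD gap, roughly equal at 0.25 SD, and 75 v 72% with no gap.

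**The case against.** The strongest objection is that a reader might infer the stratum has been excluded, so that the standard error is wrong and the 80% power is not met. The documents do not support that.

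- The article is silent. Its provision for further explanatory variables could cover public/private, and a full covariate list is commonly left to an analysis plan, which is not shown here. This stands against any claim of exclusion. It does not remove the point that the article sets a covariate policy under which a design factor is left to need or to search.
- Baseline adjustment is specified, and it absorbs most of a stable public/private gap. This stands: the 12-point loss belongs to the listed t-tests and ANOVA, not to the baseline-adjusted model.
- No public/private difference in QOL-AD is given. This stands: without one there is no loss.
- Balance of 6:6 and 3:3 is assumed, since no blocking is stated. This stands for the claim of an overstated standard error. Under unblocked allocation the test is not conservative, and the argument for the stratum term is precision when the gap is large.
- The power statement does not rely on stratification. This stands: no stated figure is shown to be wrong.

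**Conclusion.** The point holds in a limited, conditional form and is minor. Units are randomised within public/private strata, and the stated analysis does not pre-specify that factor. Given a real gap and balance within strata, analyses without it are conservative. The loss is about 2 to 12 points of power for unadjusted comparisons at a gap of 0.25 to 0.5 SD. For the baseline-adjusted model it is about 0 to 3 points, reaching 3.6 (77.4 − 73.8) only with the largest gap and the weakest correlation. These sizes rest on the assumed gap, the assumed baseline correlation of 0.3 to 0.7, 14 residents per unit, and the gap being added to an ICC of 0.1. With no gap, nothing is lost.

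**What to change.** State in the analysis section, or in the analysis plan before unblinding, that public/private enters as a fixed effect in the multi-level models for the primary and all secondary outcomes, alongside the baseline outcome and a random unit effect. It should not be left to the search for nuisance variables. It would also help to state whether allocation within each list is blocked.

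The variable is already recorded for allocation. The cost is one of about 16 degrees of freedom: under 1 point of power if there is no gap and strata are balanced, or about 3 points if there is no gap and allocation within lists is unblocked. The sample size need not change.
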